## Methods and analysis

### Study design

A two-arm, single-blinded, individual randomised controlled trial with mixed-methods process monitoring and evaluation is being carried out to evaluate the effectiveness of intervention. The participants are recruited from a rural subdistrict, randomised into intervention and control arms, on a 1:1 allocation ratio.

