### Sample size calculations

The power calculations are based on one primary outcome, that is, mother–child interaction on OMCI tool^22^ at 12 months’ postpartum. The scoring of tool is based on the frequency of the occurrence of responsive behaviours of mother with higher scores indicating more responsive interactions. The effect size for the present study was estimated based on the findings of a similar study conducted in Pakistan, where OMCI was used as one of the outcomes to evaluate the effect of responsive stimulation intervention on caregiver–child interaction at 12 and 24 months postpartum.^8^ The findings of the study showed mother–child dyads receiving responsive caregiving intervention had significantly higher mean scores on OMCI at 12 months (mean 32.3 (SD: 8.3) vs mean 27.1 (SD: 8.2), p<0.0001) than those who were allocated to control arm. Moreover, repeated-measures analysis showed that effects were sustained at 24 months. As the effect sizes for OMCI in Yousafzai *et al* 2015’s study ranged between 0.6 and 0.9; therefore, a conservative effect size of 0.4 (two-sides hypothesis) at 12 months post-partum was proposed in the present study. The effect size was calculated using the two-sided t-test. Assuming an effect size of 0.4, with 80% power, 0.05 significance and a two-sided hypothesis test and accounting for 20% attrition, we will need 250 caregiver–child dyads (125 in each arm).

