### Maternal secondary outcomes

Maternal distress will be measured by the *SRQ*^34^ at baseline, 6 and 12 months postpartum. SRQ is a 20-item self-report measure to detect non-specific psychological distress, developed by the WHO. Psychological distress is represented by subscales of depression/anxiety, somatic symptoms, reduced vital energy and depressive thoughts. The SRQ items are scored 0 or 1. A score of 1 indicates the presence of symptoms of psychological distress during past month and a score of 0 indicates the absence of symptoms. The maximum score indicates the presence of higher psychological distress. A score of >9 indicates increased risk of maternal distress/postpartum depression.^8 35^Caregivers’ health-related quality of life will be measured by *WHO Quality of Life (WHOQoL)-Brief version* at baseline and 12 months postpartum. WHOQoL assess the participants position in life in the context of the culture and value systems in which they live and in relation to their goals, expectations, standards and concerns. WHOQoL comprises of four domains namely physical health, psychological health, social relationships and environment. Items are rated on a 5-point Likert scale, where 1 represents ‘disagree’ or ‘not at all’ and 5 represents ‘completely agree’ or ‘extremely’.The level of social support will be measured using *Multidimensional Scale of Perceived Social Support (MSPSS)***36** will be measured baseline and 12 months’ postpartum. It includes 12 items which cover three dimensions: support from family, friends and significant other. Each item is rated on a 7-point Likert-scale (1=*very strongly disagree*; 7=*very strongly agree*). A total score is calculated by summing the responses of all items (range 12–84) with higher scores indicating higher levels of perceived social support.Caregiver’s level of functioning will be measured using *WHO Disability Assessment Schedule (WHODAS)***37** at baseline and 12 months’ postpartum. WHODAS assesses participants’ health-related difficulties in the level of functioning in six domains of life (understanding and communicating; moving and getting around; attending to one’s hygiene, dressing, eating and staying alone; interacting with other people; domestic responsibilities, leisure, work and school and joining in community activities, participating in society) over the past 30 days.*Maternal financial empowerment*: women’s empowerment will be measured at baseline and 12 months postpartum, using a questionnaire consisting of: (a) two items previously used in the same population^38^ that assess financial empowerment (ie, whether a woman is given a lump-sum of money for day-to-day expenses and whether she can make independent decisions about its use). Women who answer ‘yes’ to both items on financial empowerment will be classified as ‘empowered’.Utilisation of healthcare will be measured by CSRI adapted for perinatal population of Pakistan, at 12 months postpartum.^32^

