### Statistical analysis

The findings will be reported according to the Consolidated Standards of Reporting Trials guidelines for randomised controlled trial^39^ (figure 1). This will include the flow of research participants through each stage of the trial, including the number eligible, randomly assigned, receiving the intended treatment, completing the study protocol and analysed for the primary outcome. The primary analyses will be on intent-to-treat basis consisting of all participants included according to the arms in which they are randomised and secondary analyses will be based on per-protocol population.

For the analysis of the primary outcome (caregiver–child interaction across two-arms at 12 months postpartum), a linear regression model will be employed with treatment as the sole predictor. In addition, adjusted linear model analysis will be performed with the prespecified covariates (gender of infant, mother’s education and severity of mothers’ psychosocial distress measured using SRQ) measured at baseline being added into the above linear model. The crude and adjusted mean differences in the primary outcome together with its 95% CIs at 12 months will be derived from the linear models. In addition, subgroup analysis of primary endpoint will be performed on the above prespecified covariates.

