Analysis of secondary continuous outcomes with single follow-up measurement will be done in a similar fashion as the primary endpoint analysis. Analysis of secondary continuous outcomes with repeated follow-up measurement will be performed using a linear mixed model with treatment visit, interaction between treatment and visit as fixed effects, the baseline value of the outcome as covariate, if it is available and subject as random effects. The analysis of binary outcomes will also use a generalised linear/mixed model depending on whether there will be a repeated measurement. ORs with their 95% CIs will be derived from the generalised linear/mixed model analysis. Missing primary outcome and secondary outcomes with a single measurement will not be imputed; whereas, missing secondary outcomes with repeated measurements will be imputed in sensitivity analysis using the last observation carried forward strategy. Missing baseline covariates will be imputed using simple imputation methods in the covariate adjusted analysis based on the covariate distributions in the sample. For a continuous variable, missing values will be imputed from random values from a normal distribution with mean and SD calculated from the available sample. For a categorical variable, missing values will be imputed from random values from a uniform distribution with probabilities *P*_1_, *P*_2_, … and *P*_k_ from the sample. Seed for the imputation will be set as the date of data analysis. The study is powered to make a single comparison in the primary outcome at 12 months only. All analyses will be described in detail in the statistical analysis plan. SAS V.9.4 and SPSS V.21 will be employed for the statistical analyses.

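### WHOQoL, MSPSS and WHODAS have a baseline and one follow-up, but the stated 12-month models leave the outcome's own baseline out

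*Protocol article*

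**What the plan says.** Table 2 of the protocol article schedules WHOQoL, MSPSS and WHODAS at baseline (third trimester) and at 12 months, with nothing in between. The Maternal secondary outcomes section agrees: WHOQoL is taken "at baseline and 12 months postpartum. WHOQoL assess the participants position in life", MSPSS "will be measured baseline and 12 months’ postpartum", and WHODAS at the same two points. All three are continuous scores with one follow-up.

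The Statistical analysis section gives two rules for continuous secondary outcomes:

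- One follow-up: "Analysis of secondary continuous outcomes with single follow-up measurement will be done in a similar fashion as the primary endpoint analysis". The primary analysis is a linear model with treatment as its only term, plus an adjusted model that adds the "prespecified covariates (gender of infant, mother’s education and severity of mothers’ psychosocial distress measured using SRQ) measured at baseline".
- Repeated follow-up: a linear mixed model that includes "the baseline value of the outcome as covariate, if it is available".

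The same section says the trial is powered for the single primary comparison only and leaves fuller detail to a statistical analysis plan. The Hypotheses section labels the secondary hypotheses exploratory.

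**The concern.** The primary template was built for an outcome that cannot have a baseline: OMCI scores a mother playing with her infant, and at baseline the infant is not yet born. Carried over to three maternal scales that do have a baseline, the template drops a covariate the trial already collects. The plan clearly knows the technique, because its next sentence applies it to repeated outcomes such as SRQ. The article gives no reason why SRQ should be adjusted for its own baseline while WHOQoL, MSPSS and WHODAS, taken at the same time point, should not.

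Two things are at stake. The confidence intervals for these scales will be wider than they need be, in a trial with no power reserved for them. And if the arms differ by chance at baseline on a scale, part of that difference stays in the 12-month estimate. Quality of life is named in the secondary hypotheses, and social support (MSPSS) is also a proposed mediator.

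**Working it through.** **Inputs from the protocol article.** Sample size calculations: "Assuming an effect size of 0.4, with 80% power, 0.05 significance and a two-sided hypothesis test and accounting for 20% attrition", and "we will need 250 caregiver–child dyads (125 in each arm"). Study design: "randomised into intervention and control arms, on a 1:1 allocation ratio".

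**Inputs assumed, because the article gives none.** Correlation r between a scale's baseline and 12-month values: 0.3 to 0.6. Treatment effect on these scales: 0.3 SD.

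**Step 1: reproduce the plan's own figure.** For a two-sided t-test at d = 0.4, α = 0.05 and 80% power, n = 99.08, so 100 per arm; 100/0.8 = 125 per arm, 250 in total. The normal approximation gives 99 per arm; 99/0.8 = 123.75, so 124 per arm and 248 in total. The stated 250 is right and implies 100 completers per arm.

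**Step 2: gain over the treatment-only model.** Adding the own baseline multiplies the residual SD by √(1 − r²). In SD units, SE = √(1 − r²) × √(2/100), and power = Φ(0.3/SE − 1.96).

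| r (assumed) | Residual variance | SE | 95% CI half-width | Power at 0.3 SD |
|---|---|---|---|---|
| 0 (baseline left out) | – | 0.141 | 0.277 | 56.4% |
| 0.3 | −9% | 0.135 | 0.264 | 60.4% |
| 0.5 | −25% | 0.122 | 0.240 | 68.8% |
| 0.6 | −36% | 0.113 | 0.222 | 75.5% |

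The t-distribution gives 56%, 60%, 68% and 75%. At r = 0.5 the gain equals having 100/(1 − 0.25) = 133 completers per arm without adjustment.

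**Step 3: gain over the planned adjusted model.** That model already holds baseline SRQ, which may stand in for part of the missing baseline. Assume SRQ correlates a = 0.2 to 0.3 with the 12-month outcome and b = 0.4 to 0.6 with the outcome's own baseline. Infant gender and education are ignored here. Then

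R² with both = (r² + a² − 2rab)/(1 − b²), and SE ratio = √[(1 − R²)/(1 − a²)].

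Example, r = 0.5, a = 0.2, b = 0.4: R² = (0.25 + 0.04 − 0.08)/0.84 = 0.25; SE ratio = √(0.75/0.96) = 0.884.

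| r (assumed) | SE ratio over the four a, b pairs | Further fall in SE |
|---|---|---|
| 0.3 | 0.970–0.988 | about 1–3% |
| 0.5 | 0.875–0.908 | about 9–13% |
| 0.6 | 0.791–0.836 | about 16–21% |

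**Step 4: chance imbalance.** Without the baseline term, a baseline difference of δ SD shifts the treatment-only estimate by about r × δ. A difference of one standard error (√(2/100) = 0.141 SD) at r = 0.5 shifts it by 0.5 × 0.141 = 0.07 SD. Over repeated randomisations these shifts average to zero, which is why the issue is precision and not bias.

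**The case against.** The strongest reply is that the article says similar, not identical, and defers detail to an analysis plan that is not shown. That plan may well add the baseline term, and nothing in the article forbids it. This limits how certain one can be about the analysis that will be run. It does not cure the wording: the article states one rule for each class of outcome and attaches the baseline term to only one of them, so an analysis plan that follows it literally carries the gap forward.

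The second reply is about size. The outcomes are exploratory, the correlations are assumed, and baseline precedes the 12-month visit by more than a year in women selected for SRQ of at least 9, so low correlations are plausible. Baseline SRQ is already in the adjusted model. All of this stands: at r = 0.3 the gain over that model is trivial.

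A reader might also infer more than the article supports:

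- **That maternal empowerment has the same fault.** It is a binary outcome under a separate rule that names no covariates, so baseline is neither included nor excluded. Adjustment there would also change the target to a conditional odds ratio and typically widen its standard error even as power rises, so the precision argument does not carry over.
- **That the treatment-only model should not lead for OMCI.** Both OMCI models are prespecified and reported, and the crude one matches the t-test used for the sample size. Preferring the other is a trade-off, not a correction.
- **That the secondary estimates would be biased.** Randomisation protects them on average.

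**Conclusion.** The point holds for the WHOQoL domains, MSPSS and WHODAS. As written, both models omit a baseline that is collected and that the same section uses for repeated outcomes. On the treatment-only model, power for a 0.3 SD effect is 56%, against about 60–75% with the baseline included, given 100 completers per arm and an assumed r of 0.3 to 0.6. Against the SRQ-adjusted model the benefit runs from negligible at r = 0.3 to material at r = 0.5 and above, and it rests on further assumed correlations. The consequence is avoidable imprecision and exposure to chance imbalance on exploratory outcomes. The primary outcome and the 250 dyads are not affected. It is worth changing because the improvement is almost free, not because the trial's main conclusion depends on it.

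**What to change.** In the Statistical analysis section, or in the analysis plan that details it, extend the phrase "the baseline value of the outcome as covariate, if it is available" to continuous secondary outcomes with a single follow-up. For the WHOQoL domains, MSPSS and WHODAS, name the estimate from the model with treatment and the scale's own baseline as the main one. Keep the own baseline in the model that adds infant gender, education and SRQ, and show the treatment-only difference as supportive. The words on availability leave infant outcomes measured only at 12 months unchanged.

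The cost is a line of text and one model term; no new data are needed. A missing baseline score would fall under the plan's existing imputation rule for baseline covariates. The change should be fixed before anyone sees outcome data by arm.

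### WHOQoL, MSPSS and WHODAS are collected at baseline, but the stated model for single-follow-up outcomes does not use those values, so an otherwise valid analysis loses precision

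*Protocol article*

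**What the plan says.** Maternal secondary outcomes and Table 2 (Schedule of assessments) place WHOQoL, MSPSS and WHODAS at baseline and at 12 months postpartum, and at no other visit. Each therefore has one baseline value and one follow-up value. Among the maternal scales only SRQ is followed up twice, at 6 and 12 months. OMCI, the primary outcome, is measured at 12 months only and has no baseline.

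The Statistical analysis section then sets these rules:

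- Continuous secondary outcomes with one follow-up: "Analysis of secondary continuous outcomes with single follow-up measurement will be done in a similar fashion as the primary endpoint analysis".
- The primary analysis: "a linear regression model will be employed with treatment as the sole predictor", followed by an adjusted model that adds "prespecified covariates (gender of infant, mother’s education and severity of mothers’ psychosocial distress measured using SRQ) measured at baseline".
- Continuous secondary outcomes with repeated follow-up: a linear mixed model that includes "the baseline value of the outcome as covariate, if it is available".
- Binary outcomes: a generalised linear or mixed model, with no covariates listed.

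Financial empowerment is also collected twice ("women’s empowerment will be measured at baseline and 12 months postpartum"), but it is classified as yes or no and so falls under the binary rule.

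**The concern.** The single-follow-up rule borrows a model built for an outcome that cannot have a baseline and applies it to three scales that do. Followed as written, neither the crude nor the adjusted model for WHOQoL, MSPSS or WHODAS contains the score taken at entry. A scale's own earlier value is usually among its best predictors, so leaving it out makes the standard error larger than it need be. A chance difference between arms at entry also carries through to the 12-month estimate in proportion to the correlation.

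The protocol already accepts the principle, since it adjusts SRQ for its own baseline. The number of later visits is no reason to use a baseline value for one maternal scale and not for the others.

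At stake is the precision of several named secondary outcomes. Quality of life is part of the secondary hypotheses, and social support is also proposed as a mediator. The trial is powered only for OMCI, so precision on these scales is not plentiful.

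**Working it through.** **Inputs from the protocol.** The Sample size calculations section uses a standardised effect of 0.4, power of 80% and a two-sided 5% level. Its resulting total is stated as: "accounting for 20% attrition, we will need 250 caregiver–child dyads (125 in each arm". Study design: "randomised into intervention and control arms, on a 1:1 allocation ratio".

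**Reproducing the stated sample size.**
- Normal approximation: n per arm = 2 × (1.960 + 0.842)² / 0.4² = 98.1, so 99. Dividing by 0.8 gives 124 per arm, 248 in total.
- t-test: n per arm = 99.08, so 100. Then 100 / 0.8 = 125 per arm, 250 in total.

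The stated 250 is reproduced, and about 100 evaluable mothers per arm is the right basis for what follows.

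**Input not in the documents.** The correlation r between a scale's baseline and its 12-month value is not given, so a range is assumed.

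**Gain over the treatment-only model.** Adding the own baseline multiplies the residual variance by 1 − r². Hence:
- standard error ratio = √(1 − r²)
- equivalent unadjusted n per arm = 100 / (1 − r²)
- detectable difference at 80% power = 2.802 × √(2/100) × √(1 − r²), in SD units. This is 0.396 without the baseline.

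| Assumed r | SE ratio | SE reduction | Equivalent n per arm | Detectable difference (SD) |
|---|---|---|---|---|
| 0.2 | 0.980 | 2% | 104 | 0.388 |
| 0.3 | 0.954 | 5% | 110 | 0.378 |
| 0.5 | 0.866 | 13% | 133 | 0.343 |
| 0.6 | 0.800 | 20% | 156 | 0.317 |

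**Gain over the SRQ-adjusted model.** Let r be the correlation of the outcome with its own baseline, s that of the outcome with baseline SRQ, and b that between the two baselines. With both covariates, R² = (r² + s² − 2rsb) / (1 − b²). The SE ratio against SRQ alone is √[(1 − R²) / (1 − s²)]. All three correlations are assumed. Infant gender and education are left out for simplicity.

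- r = 0.5, s = 0.3, b = 0.5: R² = (0.25 + 0.09 − 0.15) / 0.75 = 0.253. SE ratio = √(0.747 / 0.91) = 0.906, a reduction of about 9%.
- r = 0.4, s = 0.2, b = 0.4: R² = 0.136 / 0.84 = 0.162. SE ratio = √(0.838 / 0.96) = 0.934, about 7%.
- r = 0.3, s = 0.2, b = 0.5: R² = 0.07 / 0.75 = 0.093. SE ratio = √(0.907 / 0.96) = 0.972, about 3%.

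**Chance imbalance.** The standard error of a baseline difference at 100 per arm is √(2/100) = 0.141 SD. A difference larger than 0.2 SD in either direction (0.2 / 0.141 = 1.41 standard errors) has probability about 0.16. Given a difference of 0.2 SD, the treatment-only estimate is expected to move by r × 0.2, which is 0.06, 0.10 or 0.12 SD for r = 0.3, 0.5 or 0.6. The SRQ-adjusted model would remove part of this, to the extent that SRQ is correlated with the scale.

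**The case against.** **The wording is not closed.** The rule asks for a similar analysis, not an identical covariate list, and the template outcome could not have supplied a baseline term. Detail is deferred to a statistical analysis plan that is not shown, and a plan that added the baseline would not clash with this sentence. This softens the point but does not remove it. The protocol does state the models and covariates, and the very next rule names the own baseline for repeated follow-up only. On its plain reading the text leaves it out here.

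**The gains depend on assumptions and on the comparator.** The larger figures are against the treatment-only model, whereas an SRQ-adjusted model is also planned. Baseline is in the third trimester, in women selected on their SRQ score, and follow-up is a year after birth, so a low correlation cannot be excluded. At r = 0.2 the reduction is only 2%. This stands, and the size should be read as a range.

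**Empowerment.** A reader might infer that empowerment suffers the same loss, with a wider interval. The documents do not support that. The binary rule lists no covariates at all, so the baseline is unmentioned rather than excluded. In a logistic model, adding a prognostic covariate does not narrow the interval for the odds ratio. The figures above do not apply to it.

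**Consequence.** The secondary hypotheses are labelled exploratory, and the trial is powered for a single comparison on OMCI. This also stands.

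**Conclusion.** The point holds for three continuous secondary scales: the WHOQoL domains, MSPSS and WHODAS. As written, the plan collects their baselines and then leaves them out of both stated models.

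The cost is efficiency. Against the treatment-only model the standard error is larger than it need be, by an amount that the own baseline would cut by about 5%, 13% or 20% at assumed correlations of 0.3, 0.5 or 0.6. Against the SRQ-adjusted model the saving is smaller, about 3% to 9% in the assumed examples. These figures rest on about 100 evaluable mothers per arm and on correlations that the documents do not give.

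A reader might infer that the planned estimates are biased or invalid. They are not. Randomisation makes the crude estimate unbiased, and its confidence interval already allows for chance imbalance. The shift of 0.06 to 0.12 SD arises only conditionally, when an imbalance of 0.2 SD has occurred. The primary outcome and the sample size are untouched. This is a worthwhile improvement to a stated model, not the repair of a wrong one.

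**What to change.** Extend the protocol's own baseline-covariate phrase to outcomes with a single follow-up. Suggested text: *Continuous secondary outcomes with a single follow-up will be analysed by linear regression on treatment and, where it was measured, the baseline value of the same outcome (WHOQoL domains, MSPSS, WHODAS). The other prespecified covariates are added in the adjusted model.*

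Outcomes with no baseline (BSID-III, ASQ3, Home inventory, anthropometry) stay as written.

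For empowerment, baseline status can be added to the logistic model for power and control of imbalance. The text should then say that the odds ratio is conditional on baseline status, and should not promise a narrower interval.

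The cost is one sentence in the protocol or the statistical analysis plan, fixed before the outcome data are analysed. No new data, visits or participants are needed.

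### Missing OMCI scores are left out of the primary analysis, and the article names no sensitivity analysis for them; the one method it names, LOCF, applies to other outcomes and is weaker than the planned mixed model

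*Protocol article*

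**What the plan says.** All references are to the protocol article.

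- **Sample size calculations.** The target is 250 dyads, 125 per arm: "Assuming an effect size of 0.4, with 80% power, 0.05 significance and a two-sided hypothesis test", after allowing for 20% attrition.
- **Table 2.** OMCI has one assessment, at 12 months postpartum. SRQ is also taken at baseline and 6 months. WHO-QoL, MSPSS and WHODAS are taken at baseline and 12 months.
- **Statistical analysis, population.** The primary analysis is on an "intent-to-treat basis consisting of all participants included according to the arms in which they are randomised". The model is a linear regression on treatment alone. A second model adds infant gender, mother's education and baseline SRQ, and both mean differences are reported.
- **Statistical analysis, missing data.** "Missing primary outcome and secondary outcomes with a single measurement will not be imputed". By contrast, missing values of secondary outcomes with repeated measurements "will be imputed in sensitivity analysis using the last observation carried forward strategy". Missing baseline covariates in the adjusted model are filled by random draws, and "Seed for the imputation will be set as the date of data analysis".
- **Statistical analysis, detail.** Full description is left to a statistical analysis plan, which is not shown.

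**The concern.** With a single measurement and no imputation, a dyad without the 12-month visit contributes nothing to the primary model. The crude difference is then unbiased for all randomised dyads only if, within each arm, loss is unrelated to the score that would have been observed. The adjusted model relaxes this, but only for its three baseline covariates. It cannot take in the 6-month SRQ, which is measured after randomisation and which the article lists among its potential mediators.

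The article gives reasons to take informative loss seriously. It names retention to 12 months as a challenge during the pandemic. OMCI needs a live observation, while telephone replacement is described only for intervention sessions. It also cites strong evidence that interaction quality is associated with maternal depression, so loss driven by distress would be loss related to the outcome. The session programme, from the seventh month of pregnancy to 48 weeks postnatal, exists in one arm only, so reasons for loss could differ by arm.

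At stake is the one comparison that the trial is powered for. The same scores also feed the cost-effectiveness analysis.

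LOCF does not help with OMCI, and it is a step down for the outcomes it covers. The planned mixed model uses all available follow-up and is valid when missingness depends on observed data. LOCF instead assumes that nothing changes between 6 and 12 months. It would carry forward the 6-month SRQ, a diarrhoea count with a 2-week recall, and a 6-month immunisation status that cannot reflect doses falling due later.

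**Working it through.** **1. Reproduce the plan's figure.** Inputs from Sample size calculations: effect 0.4 SD, 80% power, two-sided 0.05, t-test, 20% attrition. The two-sample t-test needs 99.08, so 100 per arm. 100 / (1 − 0.20) = 125 per arm, 250 in total. The stated figure is reproduced exactly.

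**2. What the primary model will hold.** 0.80 × 250 = 200 dyads analysed, 50 not. Power with 100 completers per arm is 80.4%, against 88.3% if all 125 per arm were observed. The calculation already assumes an analysis of completers, so the question is bias and description, not power.

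**3. Bias under an assumed departure.** Let f be the share missing in the intervention arm, and delta the amount in SD by which lost intervention mothers would score below completers. Assume control losses are at random. The complete-case difference then overstates the difference in all randomised by f × delta. The article gives no figure for delta; the values are assumptions.

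| delta (SD) | bias at f = 0.20 | share of 0.4 SD |
|---|---|---|
| 0.25 | 0.05 | 12.5% |
| 0.50 | 0.10 | 25% |
| 0.75 | 0.15 | 37.5% |

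**4. Setting infant deaths aside.** Study settings gives infant mortality of 55 per 1000 live births in Rawalpindi. 250 × 0.055 = 13.75, about 14. This is a general-population rate and only a rough guide here. These dyads have no OMCI score to recover. If they are among the 50 losses, 36 of 236 remaining dyads are missing: 36 / 236 = 0.153. The bias becomes 0.153 × 0.25 = 0.04 SD to 0.153 × 0.75 = 0.11 SD, about 10% to 29% of the design effect.

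**5. Tipping point.** With 100 completers per arm, SE = √(2/100) = 0.141 SD, and the smallest significant difference is 1.96 × 0.141 = 0.277 SD. With the SE held fixed, an observed 0.40 SD loses significance at delta = (0.40 − 0.277) / 0.20, about 0.61 SD. With f = 0.153 it does so at about 0.81 SD.

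**The case against.** **The analysis plan may contain the missing check.** This is fair. The article rules out imputing OMCI but does not rule out weighting, bounds or a comparison of lost with retained dyads. A reader might infer that the trial has no sensitivity analysis for its primary outcome; the document supports only that this article names none. The point is still more than omitted detail, because the article itself fixes the no-imputation rule and places its one named missing-outcome method on secondary outcomes.

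**The adjusted model is already a partial safeguard.** This stands. It is valid if missingness depends only on arm and its three covariates, and multiple imputation on those same covariates would add little. The gain would come from the other baseline scales, the 6-month SRQ and the delta shift.

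**The reference to all participants concerns allocation.** Largely fair. The article also commits to reporting numbers randomised and numbers analysed, so the loss is not hidden. What remains is a wording correction.

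**Two stronger readings do not hold.**
- A reader might infer that LOCF freezes the antenatal SRQ of women selected for high scores. The text applies LOCF to repeated measurements and treats baseline as a covariate, so a missing 12-month SRQ would take the 6-month value. Baseline carry-forward is not stated.
- A reader might infer that only the intervention arm involves contact. Under Treatment as-usual, both arms receive Lady Health Worker visits in equal number, and assessments are the same. Only the sessions differ, so differential loss is plausible but not documented.

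**LOCF and the seed are secondary.** LOCF sits behind a mixed model for outcomes whose hypotheses are labelled exploratory. The seed touches only missing baseline covariates in the adjusted model, which should be few. Both points are minor beside the one on OMCI.

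**Conclusion.** The point holds as an improvement that should be made, not as an error that invalidates the design. About 50 of 250 randomised dyads would be absent from the primary model at the planned attrition, and the article names no examination of what their absence could do. Under the assumed one-arm deltas of 0.25 to 0.75 SD, the bias is 0.05 to 0.15 SD, or about 0.04 to 0.11 SD with infant deaths set aside. These figures show scale only. The document supports neither a particular delta nor a direction, and an observed effect of exactly 0.40 SD would need a delta of about 0.61 SD or more to lose significance. The sample size of 250 is correct and does not change. LOCF is a poor choice of sensitivity method for the repeated outcomes, since it is weaker than the main model it is meant to test.

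**What to change.** 1. Keep the complete-case model as primary, but describe its population as randomised dyads with an observed OMCI score, analysed as allocated.
2. Prespecify one sensitivity analysis for OMCI: multiple imputation by arm, using the baseline scales (SRQ, WHO-QoL, MSPSS, WHODAS), mother's education and the 6-month SRQ, followed by a delta shift carried to the tipping point.
3. Do not impute dyads with fetal or infant death. Report them by arm.
4. For repeated secondary outcomes, drop LOCF. Rely on the mixed model under missing-at-random, with a delta-adjusted imputation as the sensitivity analysis.
5. Minor: fix the covariate-imputation seed in advance as a number. A seed tied to the analysis date lets the imputed values change with the day of the run.

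The variables are already scheduled for collection and no further participants are needed. The cost is wording, modest programming and a sensitivity result that may be less favourable than the headline. To be credible, the choices should be fixed before outcome data are seen by arm. If the analysis plan already contains an OMCI sensitivity analysis, only items 1, 4 and 5 and the handling of deaths need checking against it.
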